#### Exclusion criteria

Pregnant or breastfeeding.Underlying primary immunodeficiency.Received or likely to receive intravenous/subcutaneous immunoglobulin (IVIg/SCIg).Projected treatment is likely to involve plasma exchange.Contraindication to receipt of a COVID-19 vaccine.Intolerance of or previous allergic reaction to tetanus vaccination.If switching immunosuppressive therapies following enrolment absolute neutrophil count must be above 0.5×10^9^/L at screening.

Bone marrow transplant group (Group 2)

#### Inclusion criteria

Adult aged ≥18 years with a medical condition included in table 1.Undergone a BMT for a haematological malignancy in the previous 9 months.Previously received at least three post-BMT doses of any licensed COVID-19 vaccine as per current standard of care post-transplant guidelines.^16^Voluntary written informed consent.

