## Abstract

**Introduction:**

Immunosuppression is associated with an increased risk of delayed SARS-CoV-2 viral clearance, severe COVID-19 and related death. This heterogeneous group of affected patients includes but is not limited to those with a haematological malignancy, people on immunosuppressive therapy for the treatment of autoimmune/inflammatory diseases and those following bone marrow transplantation (BMT). Immunosuppression is associated with decreased rates of anti-spike IgG seroconversion following COVID-19 vaccination. While clinical guidelines have been established to guide vaccination pre-splenectomy and post-BMT, there are limited data to guide timing of COVID-19 or other booster vaccines in adults commencing new or intensified moderate to severe immunosuppression. The comparison of immunity-boosting regimens for COVID-19 upon initiation of immunosuppressive therapy (CIRCUIT) study was designed to address this knowledge gap. CIRCUIT investigates whether administration of a third (or subsequent) COVID-19 booster vaccine ≤2 weeks prior to immunosuppression provides greater anti-spike IgG-mediated immunity than a booster given 24 weeks after new or intensified immunosuppression, that is, week 24 timepoint (Group 1; n=280). Additionally, the research will investigate whether giving a fourth post-BMT COVID-19 booster vaccine at 9 months post-transplant provides greater anti-spike IgG-mediated immunity than a booster given 15 months post-transplant (Group 2; n=40).

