**Methods and analysis:**

The CIRCUIT study is an open-label, multicentre randomised clinical trial. Participants will be randomised 1:1 to receive either an additional COVID-19 booster ≤2 weeks pre-immunosuppression and a diphtheria/tetanus toxoids (DT) booster at 24 weeks following new or intensified immunosuppression (week 24 timepoint) or receive a DT booster ≤2 weeks pre-immunosuppression and an additional COVID-19 booster at week 24 (Group 1). Group 2 participants who underwent autologous or allogenic BMT in the last 9 months will be randomised 1:1 to either receive a fourth post-BMT COVID-19 booster at 9 or 15 months post-transplant. The primary outcome will be the integrated time-weighted area under the curve anti-SARS-CoV-2 neutralising antibody (NAb) response over 12 months from a SARS-CoV-2 booster as assessed by a high-throughput SARS-CoV-2 NAb platform assay. Key secondary outcomes of the CIRCUIT randomised control trial will include safety and generation of SARS-CoV-2 antigen specific T and B cell responses.

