Prior to the COVID-19 pandemic there were limited evidence-based national or international guidelines around the timing of adult booster vaccinations for those with moderate to severe immunosuppression apart from splenectomy and BMT. In response to the COVID-19 pandemic, guidelines advising COVID-19 vaccinations including booster vaccines should be given at least 2 weeks prior to rituximab therapy emerged based on evidence of improved anti-spike IgG seroconversion in patients who had received COVID-19 vaccines 2–4 weeks prior to B-cell depletion.^17^,^19^ However, data relating to other forms of immunosuppression are lacking, and for this reason, the CIRCUIT study was conceived to determine the optimal timing of COVID-19 booster vaccines in two adult patient groups; Group 1: adults commencing new or intensified moderate-to-severe immunosuppression for the treatment of a haematological malignancy or an autoimmune/inflammatory disease and Group 2: adults who have undergone allogenic or autologous BMT in the previous 9 months. Due to a related study running concurrently in Australia,^20^ people with HIV infection and solid organ transplant recipients were not included in the CIRCUIT study.

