### Explanation for choice of comparator

Group 1 participants will be randomised to receive either a baseline (week 0) COVID-19 booster prior to commencing new or intensified immunosuppressive therapy and a DT booster at week 24 (Arm A) or a baseline DT booster and a week 24 COVID-19 booster (Arm B).

Participants in Group 2 will have undergone a BMT in the previous 9 months and received three post-BMT COVID-19 vaccines. These participants will be randomised to either receive their fourth post-BMT COVID-19 vaccine at baseline (week 0) (Arm C) or at week 24 (Arm D).

Due to the evolving nature of COVID-19 vaccine development, the study will accept any COVID-19 vaccine licensed for use in Australia. Due to established guidelines on post-BMT vaccination including diphtheria and tetanus, only COVID-19 boosters will be studied in Group 2.^16^

The DT vaccine was selected as the comparator for the COVID-19 vaccine. The DT vaccine is protein-based and stimulates an immune response via a different mechanism to that of currently available mRNA-based COVID-19 vaccines. The study will assess whether the findings that relate to the optimal timing of the COVID-19 booster also apply to more traditional protein-based vaccines. If this is found to be the case, then the study results may have broader implications for vaccinology and optimal clinical guidelines.

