### Objectives

This study aims to evaluate the optimal timing of a COVID-19 booster vaccination in adults commencing moderate-to-severe immunosuppression for either an autoimmune/inflammatory disease or a haematological malignancy or who have undergone a bone marrow transplant in the previous 9 months. Efficacy will be assessed primarily by measuring the anti-SARS-CoV-2 neutralising antibody (NAb) response to the booster over 12 months. Other correlates of protective immunity as well as safety and quality of life will be assessed.

Delaying administration of the COVID-19 booster in the deferred arms may lead to higher numbers of breakthrough COVID-19 infections in these arms. The Data Safety Management Board (DSMB) will closely monitor on-study infections and advise the principal investigator and Protocol Steering Committee (PSC) should there be any concerns.

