### Trial design

CIRCUIT is an open-label, multicentre randomised clinical trial. Participants with a haematological malignancy or autoimmune/inflammatory disease will be randomised in a 1:1 ratio to receive either an additional COVID-19 booster pre-immunosuppression with a DT booster after 6 months of therapy or a DT booster pre-immunosuppression and an additional COVID-19 booster at 6 months. Participants at least 9 months post-BMT will be randomised in a 1:1 ratio to either receive a COVID-19 booster either following randomisation or after 6 months.

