### Randomisation

#### Sequence generation

Participants will be assigned to a study group based on their study-qualifying medical condition (table 1) using a central computer-generated randomisation sequence with a blocking factor of four created by the study statistician.

Participants in Group 1 will be stratified into one of two supra-stratum, haematological malignancy or systemic autoimmunity and then to sub-strata based on their planned treatment. Sub-strata include: haematological malignancy—chemotherapy; autoimmunity—B-cell depletion therapies; autoimmunity—anti-metabolite therapies; autoimmunity—TNFα-inhibition; autoimmunity—cyclophosphamide or alemtuzumab; autoimmunity—JAKi; autoimmunity—anti IL-17/23 monoclonal antibodies (table 1).

Group 1 participants will be randomised in a 1:1 ratio to receive either a COVID-19 booster at week 0 and a DT booster at week 24 (Arm A: immediate booster), or a DT booster at week 0 and a COVID-19 booster at week 24 (Arm B: deferred booster) (figure 1). Randomisation will be conducted using a central computer-generated random allocation algorithm using blocks and stratified by sub-strata population.

Group 2 has no sub-strata and participants will be randomised in a 1:1 ratio to receive either an immediate COVID-19 booster at week 0 (Arm C), or a deferred COVID-19 booster at week 24 (Arm D) (figure 1).

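### Group 2 has two incompatible entry rules (BMT no more than, versus no less than, 9 months ago), and neither assures the stated comparison of boosters at 9 versus 15 months

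*Protocol article*

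**What the plan says.** The Group 2 inclusion criteria require "Undergone a BMT for a haematological malignancy in the previous 9 months". Four other places use the same upper limit:

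- Abstract, Methods and analysis: "BMT in the last 9 months will be randomised 1:1 to either receive a fourth post-BMT COVID-19 booster at 9 or 15 months post-transplant"
- Background and rationale: "Group 2: adults who have undergone allogenic or autologous BMT in the previous 9 months"
- Objectives: "or who have undergone a bone marrow transplant in the previous 9 months"
- Explanation for choice of comparator: "Participants in Group 2 will have undergone a BMT in the previous 9 months and received three post-BMT COVID-19 vaccines"

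The Trial design section reverses the direction: "Participants at least 9 months post-BMT will be randomised in a 1:1 ratio".

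The abstract's Introduction states the scientific question for this group as whether "giving a fourth post-BMT COVID-19 booster vaccine at 9 months post-transplant provides greater anti-spike IgG-mediated immunity than a booster given 15 months post-transplant". The dosing schedule, however, runs on study time. Sequence generation gives an "immediate COVID-19 booster at week 0 (Arm C), or a deferred COVID-19 booster at week 24 (Arm D"), and the Trial design section places the immediate booster just after randomisation and the deferred one 6 months later. No section ties week 0 to month 9 after transplant.

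**The concern.** Time since transplant is the factor Group 2 is meant to study, and the entry rule determines it. One rule is a maximum and the other a minimum, so a site with a patient 8 or 11 months after transplant gets opposite answers depending on which section it reads. Both statements are current text.

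Even if one rule were chosen as written, the stated contrast would not follow. With boosters at week 0 and week 24, the time since transplant at vaccination is whatever it was at entry, plus 0 or 24 weeks. An upper limit lets it fall below 9 months; a lower limit with no ceiling lets it run well above. The result could then be reported as a comparison of 9 with 15 months when the boosters were given at other times, and that label is the part clinicians would use for scheduling after BMT.

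**Working it through.** **1. The two rules side by side.** Let *t* be months since BMT at randomisation.

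- Rule A (inclusion criterion; also the abstract's Methods and analysis, Background and rationale, Objectives, and Explanation for choice of comparator): *t* ≤ 9.
- Rule B (Trial design): *t* ≥ 9, no upper limit.
- Both together: *t* = 9 only.

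**2. Booster timing that each rule produces.** Inputs: week 0 and week 24 from Sequence generation; one month taken as 30.44 days.

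Deferral = 24 × 7 = 168 days; 168 / 30.44 = 5.52 months. Immediate booster at *t*; deferred booster at *t* + 5.52.

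| Entry (*t*, illustrative) | Allowed by | Immediate, months | Deferred, months |
|---|---|---|---|
| 7 | A | 7.0 | 12.5 |
| 8 | A | 8.0 | 13.5 |
| 9 | A and B | 9.0 | 14.5 |
| 12 | B | 12.0 | 17.5 |
| 18 | B | 18.0 | 23.5 |

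The gap between arms is always about 5.5 months. The absolute timing comes close to 9 versus 15 only when entry is at about 9 months.

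**3. Whether the choice of rule can change who is eligible.** Group 2 patients must already have had three COVID-19 doses since transplant. The article does not give the schedule for those doses, so this step rests on an assumption. Suppose they start at 6 months, when Background and rationale says general revaccination begins.

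- 4-week spacing: third dose at 6 + 56/30.44 = 7.8 months. Rule A admits people from about 7.8 to 9.0 months, fairly close to the label.
- Break-even spacing: 3 months = 91.3 days = 13.0 weeks; divided by the two intervals, 6.5 weeks. The third dose falls at 9.0 months, where Rule A closes.
- 8-week spacing: third dose at 6 + 112/30.44 = 9.7 months. Rule A admits nobody; Rule B admits these patients.

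The start date matters as well. With a start at 5 months and 8-week spacing, the third dose falls at 5 + 3.68 = 8.7 months and Rule A admits a few people again. An earlier start thus widens the Rule A window, but it also allows entry further below 9 months.

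**4. Power is not involved.** The Sample size section claims over 90% power for a 0.13 log10 difference with SD 0.12 and 40 participants. With 20 per arm, 0.13 / (0.12 × √(2/20)) = 3.43; less 1.96, this gives a normal-approximation power of 0.929. The two-sample t-test gives 0.916. The claim reproduces, and neither entry rule changes it.

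**The case against.** The strongest reply is that the two statements apply at different moments. A patient could be identified and enrolled within 9 months of transplant, then randomised on reaching 9 months. Strategies to improve adherence to intervention protocols permits screening and randomisation on the same day but does not require it. On that reading week 0 falls at about 9 months, week 24 at about 14.5, and the advertised timing makes sense. This is probably close to what was intended. But no section says it, and the abstract's sentence applies the upper limit to the people being randomised. The Trial design section would also still lack a ceiling.

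A second reply is that the full protocol, the trial design figure or the supplementary visit schedule may set a window. A missing window alone would be fair to leave to those documents. Two contradictory eligibility statements in the article's own text are a different matter, and eligibility is not something a SAP settles.

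A third reply is that the dose-spacing calculation is hypothetical, because the COVID-19 schedule after transplant is not given and the vaccines listed under general revaccination do not include COVID-19. That is correct. The calculation shows only that the choice of rule could decide eligibility, and the finding does not depend on it.

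It also stands that the consequence is limited. Both arms share the same entry rule, the deferral is the same length under either, and randomisation protects the comparison.

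**Conclusion.** The concern holds: the text is wrong as written and should be fixed. The inclusion criterion and four other sections set a maximum of 9 months since BMT, while the Trial design section sets a minimum. With boosters at study weeks 0 and 24, neither rule assures the stated 9-versus-15-month contrast.

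The effect is confined to Group 2: 40 of 320 participants (12.5%), whose analysis is presented separately. No bias in the randomised comparison and no loss of power is claimed. At stake are uniform eligibility across the five sites and how the result may be described. The contradiction rests on the wording alone. The timing table needs only the week 0 and week 24 schedule and uses illustrative entry times. The possibility that one rule admits nobody rests on the assumed COVID-19 dose schedule.

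**What to change.** Replace both wordings with one entry window centred on 9 months after BMT at randomisation. The investigators should set its width so that patients can complete three post-transplant COVID-19 doses first. Use the same wording in the abstract's Methods and analysis, Background and rationale, Explanation for choice of comparator, Objectives, Trial design and the Group 2 inclusion criteria. Since 24 weeks after 9 months is 14.5 months, the existing 9-versus-15 label is then a fair approximation.

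Report Group 2 by the actual time since transplant at each booster, so that readers can see what was compared. Adjusting for time since transplant at entry is an optional, low-cost addition.

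The cost is a short wording amendment with no change to sample size. The downside is that a narrower window may slow Group 2 recruitment.

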### Sample size

The maximum sample size is 320 participants, 280 in the systemic autoimmunity and haemato-oncology group and 40 in the BMT recipient group. This sample size is based on previously calculated integrated time-weighted AUC of live anti-SARS-CoV-2 NAb titres following two SARS-CoV-2 vaccinations in healthy adults^25^ and patients infected with COVID-19.^26 27^ SD calculated from these datasets were 0.11 log_10_ and 0.12 log_10_, respectively. Assuming an SD of 0.12 log_10_, the study will have over 90% power to detect a 0.13 log_10_ difference in time weighted AUC log_10_ change from baseline (2-alpha=5%) within each sub-stratum of 40 participants. This corresponds to a 35% difference in live virus neutralisation titre between randomised arms. Time-weighted AUC allows for varying of follow-up of participants due to missed visits, loss to follow-up or death. We conservatively estimate overall lost to follow-up to be 10% and mortality 1% balanced across randomised sub-strata.

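### The primary comparison, at about 20 per arm, should be pre-specified as adjusted for week 0 titre in Group 2 and the Group 1 sub-strata; a minor wording point is that the Group 2 study dose may be later than the fourth

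*Protocol article*

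**What the plan says.** **Analysis.** Under Statistical methods, the primary outcome is the time-weighted AUC change from baseline in log10 neutralising titre over 12 months. Arms are compared within each treatment stratum by two-sample t-tests without covariates. If baseline characteristics turn out unbalanced, regression-adjusted comparisons may be carried out. Group 2 is to be analysed separately with similar approaches where appropriate. Under Sample size, with an SD of 0.12 log10 and 40 participants per sub-stratum, "the study will have over 90% power to detect a 0.13 log_10_ difference in time weighted AUC log_10_ change from baseline". For the 40 BMT recipients, Sequence generation adds: "Group 2 has no sub-strata and participants will be randomised in a 1:1 ratio". Data collection methods provides for blood at baseline and at each on-site follow-up visit, and for the history of COVID-19 vaccination.

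**Dose number.** The abstract states the Group 2 question as "giving a fourth post-BMT COVID-19 booster vaccine at 9 months post-transplant" against 15 months, and then that participants will "receive a fourth post-BMT COVID-19 booster at 9 or 15 months post-transplant". Explanation for choice of comparator says that they have "received three post-BMT COVID-19 vaccines". The Group 2 inclusion criterion instead reads "Previously received at least three post-BMT doses of any licensed COVID-19 vaccine as per current standard of care post-transplant guidelines".

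**The concern.** With about 20 per arm, precision matters, and week 0 titre is likely to be among the strongest predictors of later titre. A change score does not use that information fully. It fixes the slope of follow-up on baseline at 1, whereas regression estimates the slope. When the true slope differs from 1, the t-test on change carries avoidable variance. An adjustment that is optional and prompted by an observed imbalance also leaves open, until the data are seen, whether an adjusted result will stand beside the main one. No criterion for imbalance is given.

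The same test and the same 40 participants apply in each of the seven Group 1 sub-strata, so the point is not peculiar to Group 2.

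The dose-number mismatch concerns what the Group 2 result can be said to describe: the timing of a fourth post-transplant dose, or of the next dose after at least three.

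**Working it through.** **Inputs from the article.** Difference 0.13 log10, SD of the change 0.12 log10, two-sided 5%, 40 participants (Sample size); 1:1 allocation, so n = 20 per arm (Sequence generation).

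**The plan's own figure.** Noncentrality = 0.13 / (0.12 × √(2/20)) = 3.426. With 38 df the critical value is 2.024 and power is 91.6% (92.9% by the normal approximation). The 95% CI half-width is 2.024 × 0.12 × √(2/20) = 0.077. The stated figure of over 90% is confirmed.

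**With adjustment.** The time-weighted AUC change is treated as mean follow-up titre minus baseline. Let r be the correlation between the two and k the ratio of follow-up to baseline SD. The documents give neither, so both are assumptions.

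- Variance of the change is proportional to k² + 1 − 2rk.
- Residual variance after regression on baseline is proportional to k²(1 − r²).
- Their ratio is k²(1 − r²) / (k² + 1 − 2rk). At k = 1 this is (1 + r)/2.

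The change SD is held at 0.12, with 37 df:

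| k | r | residual SD | power | CI half-width |
|---|---|---|---|---|
| 1 | 0.9 | 0.117 | 92.8% | 0.075 |
| 1 | 0.7 | 0.111 | 95.1% | 0.071 |
| 1 | 0.5 | 0.104 | 97.1% | 0.067 |
| 1 | 0.2 | 0.093 | 99.0% | 0.060 |
| 1.5 | 0.2 | 0.108 | 95.9% | 0.069 |
| 1.5 | 0.7 | 0.120 | 91.6% | 0.077 |
| 2 | 0.5 | 0.120 | 91.5% | 0.077 |

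The last row is the unfavourable case: r × k = 1, the true slope is 1, and the change score is already optimal.

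**Allowance for chance baseline differences.** The formula ignores the small variance cost of a random covariate. A simulation of 20,000 trials per correlation at k = 1 gave 92.3%, 94.4%, 96.7% and 99.0%, with a mean estimate of 0.130 with and without adjustment. In the unfavourable case the expected inflation is a factor of 1 + 1/36. Noncentrality becomes 3.426 / √(1 + 1/36) = 3.379 and power about 90.8%, so the worst loss shown is under one percentage point.

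**Attrition.** Sample size expects 10% lost and 1% dead. If all of these left the analysis, 20 × 0.89 = 17.8 per arm would remain. Unadjusted power is then 86.5% with 17 or 88.4% with 18; with adjustment at r = 0.7, k = 1 it is 91.3% or 92.8%. This is pessimistic, because the modified intention-to-treat set keeps partial follow-up.

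**Dose number, texts side by side.** The abstract and the comparator section describe a fourth dose after three. The entry criterion sets a minimum of three and no maximum. For Group 1 the abstract allows a third dose or any later one, which matches that group's entry minimum of two. The Group 2 objective lacks the equivalent phrase. Room for extra doses looks small: the background section puts general post-transplant revaccination from 6 months, and entry requires transplant within the past 9 months. But that section does not list COVID-19 doses, and Trial design says "Participants at least 9 months post-BMT will be randomised in a 1:1 ratio", so the window is not stated consistently.

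**The case against.** **Covariates belong in the SAP.** The article promises one before data lock and gives Group 2 only similar approaches as appropriate. But it does name a method, and no other for Group 2, so the choice can fairly be commented on. The SAP is where the change can be made.

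**The regression may be supplementary.** This stands. A reader might infer that the t-test is dropped once imbalance is seen, so that the primary analysis depends on the data. The text does not say so; the t-test is what will be done and regression what may be added.

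**The gain is hypothetical.** This stands in part. Every correlation and SD ratio is assumed, and the gain can vanish. The argument is that likely gain comes at very small cost, not that a deficit needs repair.

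**The baseline for the deferred arm is unsettled.** Outcomes measures 12 months from a COVID-19 booster, which Arm D receives at week 24. If Arm D's change were taken from week 24, the precision figures above would not carry over directly. Week 0 titre would remain a legitimate covariate because it precedes randomisation.

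**The dose criterion may be only a minimum schedule.** That may be how it works in practice, but it does not reconcile the texts. A reader might go further and infer that dose number confounds the Group 2 comparison. It does not: dose history is fixed before randomisation. Nor is the lack of a dose-count stratum a fault in a group of 40.

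**Conclusion.** The main point holds as an improvement at almost no cost, not as an error. The t-test is valid, the power statement is correct, and nothing supports a reading that the trial is underpowered or the estimate biased for want of adjustment. Pre-specified adjustment for week 0 titre would take power from 91.6% to between 92.8% and 99.0% if baseline and follow-up SDs are equal and their correlation lies between 0.9 and 0.2. It would leave power at about 91% in the least favourable case examined. It would also settle in advance whether to adjust. All of this takes the planned SD of 0.12 as given.

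The dose-number mismatch is real but minor. It affects the description of the Group 2 question and no estimate, test or power figure. How many participants enter with four or more post-transplant doses cannot be known from the article; the number is probably small.

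**What to change.** 1. In the SAP, make the primary comparison in Group 2, and likewise in each Group 1 sub-stratum, a linear regression of the time-weighted AUC change on arm and week 0 log10 neutralising titre, fitted whether or not imbalance is seen. Keep the unadjusted t-test as a supporting analysis.
2. Use the week 0 titre in both arms. Arm D's week 24 pre-booster titre is measured after randomisation and should not be the covariate.
3. In the abstract and comparator section, describe the Group 2 study dose as a fourth or subsequent post-BMT dose, following the Group 1 wording.

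The cost is one degree of freedom per comparison (38 to 37) and a phrase of text. No one is excluded, and no new sample or visit is needed, since baseline blood and vaccination history are already collected.
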